**Supplement 1: Summary of Statistical Analysis Revisions**

| IRB
Approval
Date | Change                                                                                                                                                                                                                                                                                                                                                                                                                                                                                                                                                                                                                                                                                                                                                                                                                                                                                                                                                                                                                                                                                                 | Rationale                                                                                                                                         |
|-------------------------|--------------------------------------------------------------------------------------------------------------------------------------------------------------------------------------------------------------------------------------------------------------------------------------------------------------------------------------------------------------------------------------------------------------------------------------------------------------------------------------------------------------------------------------------------------------------------------------------------------------------------------------------------------------------------------------------------------------------------------------------------------------------------------------------------------------------------------------------------------------------------------------------------------------------------------------------------------------------------------------------------------------------------------------------------------------------------------------------------------|---------------------------------------------------------------------------------------------------------------------------------------------------|
| 1/07/2013               | 
1. We added the following text to include a description for interim analysis:
 
We will evaluate the data on a yearly basis by performing a yearly interim analysis. Our primary outcome is self-reported xerostomia symptoms using the Xerostomia Questionnaire (XQ). At each interim analysis, we will examine the difference in change scores (between baseline and the end of radiotherapy or 7 weeks) of the XQ between arms. If the true acupuncture arm is less effective than other arms and this comparison is statistically significant at <0.001, we will terminate the study early (Peto method). These interim analyses will not affect the significance level of the final analysis.
 
In order to address safety concerns, at each interim analysis we will also evaluate the incidence of grade 3 or higher adverse events in each arm separately. If patients in any arm experience more than 20% patients experience grade 3 or higher adverse events that are either definitely or probably related to acupuncture treatment, we will terminate that arm early.
 | 
1. Inclusion of description for interim analyses per MD Anderson DSMB. Results of interim analyses were not shared with the investigators.
 |

## Supplement 1. Study Protocol & Statistical Analysis Plan

### Final Protocol

#### 1. SPECIFIC AIMS

Xerostomia (dry mouth) is a common problem among cancer patients who have received radiation treatment to the head and neck. Xerostomia often severely impairs quality of life (QOL), and available treatments have a low success rate. Patients suffering from radiation-induced xerostomia experience taste aberrations, dysphagia, odynophagia, difficulty sleeping and speaking, and loss of appetite. Such changes can lead to substantial nutritional deficits that can be difficult to reverse. Several pharmaceutical approaches to treatment, including saliva substitutes, chewing gum, lozenges, pilocarpine, and amifostine, have yielded limited results.

Studies conducted in the United States and Europe suggests that acupuncture is useful for treating radiation-induced xerostomia. No studies, however, have examined the use of acupuncture to reduce the severity of radiation-induced xerostomia or measured the duration of response to acupuncture treatment. Initial research conducted at The University of Texas M. D. Anderson Cancer Center (M. D. Anderson) and collaborative research at Fudan University Cancer Hospital (Fudan Cancer Hospital) in Shanghai, China, found that acupuncture can diminish symptoms in patients with xerostomia and could prevent the severity of xerostomia symptoms and improve quality of life in patients undergoing radiotherapy.

The proposed multi-center, randomized, placebo-controlled, single blind trial will examine the effectiveness of acupuncture at preventing radiation-induced xerostomia in patients undergoing radiotherapy for head and neck cancer at M. D. Anderson or nasopharyngeal carcinoma (NPC) at Fudan Cancer Hospital. Prior to receiving radiation treatment, patients will be randomized to one of three groups: Group 1 (G1) will receive true acupuncture, Group 2 (G2) will receive sham acupuncture, and Group 3 (G3) will receive standard care during the radiation treatment period. Subjective and objective measures of xerostomia will be collected prior to, during, and at the end of the radiation treatment period as well as 2-4, 5-9, and 10-15 months later, based on each patient's follow-up clinic schedule. The aims of this study are to:

#### PRIMARY AIM

1. Determine if true acupuncture is more effective than sham acupuncture or standard care for preventing radiation-induced xerostomia among cancer patients at M. D. Anderson and Fudan Cancer Hospital. The primary outcome will be self-reported xerostomia symptoms using the Xerostomia Questionnaire (XQ).

#### SECONDARY AIMS

1. Examine group differences in salivary flow rates using unstimulated and stimulated whole saliva flow rates. This will provide a more objective measure of salivary function.
2. Determine if true acupuncture is more effective than sham acupuncture or standard care for reducing the incidence of radiation-induced xerostomia.
3. Examine whether true acupuncture results in better overall quality of life than sham acupuncture or standard of care.
4. Determine acupuncture's effects on saliva-based factors including pH, buffer capacity, and viscosity as well as levels of total protein and the neuropeptides calcitonin-gene-related peptide (CGRP) and vasoactive intestinal polypeptide (VIP).
5. Examine the role of expectancy for the benefits of acupuncture in predicting outcomes. The role of expectancy as a moderator of the effects of treatment will be thoroughly examined.

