## **B. Innovation**

Since the mid-1990s, studies conducted by different investigators from both the United States (25, 31, 35, 44-47) and Europe (34, 36-41, 48, 49) have shown that acupuncture can have a

positive effect on symptoms related to radiation-induced xerostomia. Patients have reported relief in as few as 5 treatments with benefits lasting up to 3 years. Only our two studies (see sections C.8 and C.9), however, have examined whether acupuncture can prevent this often-debilitating side-effect of radiation treatment from occurring or if it can diminish the symptoms once it develops. There have also been no large, definitive, phase III placebo- controlled trials to determine whether acupuncture is an effective treatment for managing radiation-induced xerostomia.

Most previous trials of acupuncture to treat xerostomia have been single-institution studies. Furthermore, few studies have examined NPC, as it is not prevalent in Western countries, which is where all the previous research on acupuncture for xerostomia has been conducted. The proposed trial is unique in that we will extend the findings from our phase II trial and pilot placebo-controlled trial conducted at Fudan Cancer Hospital by now conducting a multi-center, placebo-controlled, phase III clinical trial of acupuncture to prevent xerostomia in patients with NPC and other head and neck cancers (mainly oropharyngeal cancer). The inclusion of a placebo control group will allow us to more definitively determine the benefits of acupuncture for preventing this difficult-to-manage side effect of radiotherapy to the head and neck. Examining the effects within two different cancer populations, at two different centers, in two different countries, will increase the generalizability of our findings. Importantly, in addition to using validated self-report measures for xerostomia accepted by the Food and Drug Administration as the “gold standard” for the approval of treatments for xerostomia, we will assess more general aspects of QOL, assess objective measures of salivary flow, and quantify changes in potential mechanisms through assessment of salivary constituents.

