Another innovative aspect of this study involves evaluation of participant expectations on outcomes. This will allow further exploration of how psychological phenomena may be related to outcomes in acupuncture research. Although well-conducted, placebo-controlled clinical trials have offered insights into the efficacy of acupuncture, the substantial effect seen in many placebo acupuncture groups presents a significant challenge in interpreting treatment results. Many studies, including several meta-analyses (50-56), have found that both real and placebo acupuncture produce statistically and clinically significant changes when compared to no treatment or standard/enhanced medical care. These findings suggest that the effect found in placebo acupuncture groups cannot be entirely attributed to either regression to the mean or natural disease processes; thus, the “non-specific” effect of acupuncture must be responsible in part for patients’ clinical response. Nevertheless, until we can parse the components that make up the “non-specific” effect, this effect, powerful as it may be, is likely to be discarded from a scientific standpoint. Years of psychological research has found that expectancy is one of the central pieces in this so-called “non-specific” effect. In particular, response expectancy, a form of outcome expectancy defined as “expectations held by the individual about one’s own emotional and physiological response” related to a situation or therapy, may produce important clinical changes (57). In a systematic review, Crow et al. (58) showed that when clinicians stated positive outcome expectations as opposed to uncertain expectations, most studies found improvements in patient self- reports of anxiety, pain, and distress.

A few studies have explored the association between expectancy and clinical outcomes in the context of acupuncture (59, 60). While these studies provided preliminary evidence that greater expectancy may produce better clinical response, none used a validated instrument to measure expectancy. In the proposed study, we will use an expectancy questionnaire that has been validated in both English and Mandarin (61). Investigating expectancy as part of the complex mind-body interactions of acupuncture care will likely yield important knowledge that

is both scientifically sound and clinically meaningful to patients who suffer from xerostomia and other distressing symptoms.

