We will also explore the association between expectancy and outcomes using information from the Acupuncture Expectancy Scale (AES). Expectancy will be assessed using the AES at baseline in the acupuncture and sham acupuncture groups and will be correlated with severity of xerostomia using the XQ (and other continuous variables) during and after radiotherapy. More complex analyses will also evaluate whether expectancy moderates outcomes. Following the procedures of Baron and Kenny (84), the evaluation of moderation involves examining the interaction between intervention condition and baseline expectancy. In a series of mixed model analyses, tests of the interaction of intervention condition with expectancy will be evaluated to determine whether baseline expectancy changes the impact of acupuncture condition on the outcome measures [i.e., determine whether acupuncture (active or inactive) is more effective based on baseline expectancy]. Changes in USFR, SSFR, and saliva constituents will also be examined as possible mediators of the effects of acupuncture on xerostomia symptoms following the procedures of Baron and Kenny (84) using generalized linear mixed model regression. The mediation effect estimate will be computed according to MacKinnon (85), who describes mediation as the difference of the intervention effect on outcome with and without the presence of the mediators, or alternatively, the product of the effect of the intervention on the mediators and the effect of the mediators on the outcome controlling for the intervention condition.

We will evaluate the data on a yearly basis by performing a yearly interim analysis. Our primary outcome is self-reported xerostomia symptoms using the Xerostomia Questionnaire (XQ). At each interim analysis, we will examine the difference in change scores (between baseline and the end of radiotherapy or 7 weeks) of the XQ between arms. If the true acupuncture arm is less effective than other arms and this comparison is statistically significant at  $< 0.001$ , we will terminate the study early (Peto method). These interim analyses will not affect the significance level of the final analysis. In order to address safety concerns, at each interim analysis we will also evaluate the incidence of grade 3 or higher adverse events in each arm separately. If patients in any arm experience more than 20% patients

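### The only method named for whether expectancy predicts xerostomia is a correlation of baseline AES with XQ that carries no site term, so it could partly reflect site if both scores differ materially between the two centres.

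*Supplement*

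**What the plan says.** Aim 5 (Final Protocol, section 1, Secondary Aims) has two halves. The first is prediction: "Examine the role of expectancy for the benefits of acupuncture in predicting outcomes". The second is moderation: "The role of expectancy as a moderator of the effects of treatment will be thoroughly examined". The aim itself names no method.

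The methods are in C.6 a, Data analysis:

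- **Status.** The work is introduced as exploratory: "We will also explore the association between expectancy and outcomes using information from the Acupuncture Expectancy Scale (AES").
- **Prediction.** "Expectancy will be assessed using the AES at baseline in the acupuncture and sham acupuncture groups", and these scores "will be correlated with severity of xerostomia using the XQ (and other continuous variables) during and after radiotherapy". No covariate, stratification or site term is attached to this correlation.
- **Moderation.** "In a series of mixed model analyses, tests of the interaction of intervention condition with expectancy will be evaluated".

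The general description of the longitudinal mixed models in C.6 a lists as covariates the baseline value of the outcome, the minimisation variables, ethnicity, education, and health and medical characteristics. Site is not on that list. It is also not among the minimisation factors in C.3, where it appears only as the level at which randomisation is run.

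On the sites, section B offers as a strength "Examining the effects within two different cancer populations, at two different centers, in two different countries". On the instrument it says "we will use an expectancy questionnaire that has been validated in both English and Mandarin". C.1 gives the enrolment split as 193 at M. D. Anderson and 242 at Fudan.

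**The concern.** Arm is randomised and expectancy is not. Running the minimisation separately at each site balances the arms within site, which protects the comparison of true with sham. It does nothing to balance AES against the determinants of XQ.

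Several things vary along the line between the centres: country, questionnaire language, tumour type (mainly oropharyngeal at one, nasopharyngeal at the other) and possibly the mode of XQ collection, since C.5 allows telephone collection for patients who cannot come to M. D. Anderson. If mean AES and mean XQ both differ between centres, a correlation over all patients is non-zero even when expectancy predicts nothing within either centre. If the between-site and within-site associations have opposite signs, a real association can be hidden.

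The moderation test has a related but narrower exposure. If AES differs by site and the true-sham effect also differs by site, then arm x AES stands in for an arm x site interaction that is not in the model.

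At stake is the interpretation of aim 5: whether a reported expectancy effect describes patients' expectations or only where they were treated.

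**Working it through.** **Inputs from the documents**

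- Evaluable patients: 100 per arm (C.6 c), so 200 in the two acupuncture arms. The planned size reproduces: 300 / (1 - 0.31) = 434.8, rounded up to 435, and 100 per arm gives power 0.807 for 0.4 SD at two-sided 0.05. The plan states no figure for aim 5.
- Site split: p = 193/435 = 0.4437, so p(1 - p) = 0.2468.

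**Assumptions.** The documents give no AES values by site and no XQ values for M. D. Anderson, so the site gaps are a range and not estimates. Let dA and dX be the site differences in AES and XQ, in within-site SD units. Take the within-site correlation as zero and two-sided alpha as 0.05.

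**Step 1: the correlation when site is ignored**

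r = p(1 - p) dA dX / sqrt[(1 + p(1 - p) dA²)(1 + p(1 - p) dX²)]

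Example with dA = dX = 0.5: r = 0.0617 / 1.0617 = 0.058.

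The numerator is a product, so r is exactly zero if either gap is zero. If the gaps run in opposite directions, r changes sign.

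**Step 2: the false-positive rate.** With m = atanh(r) × sqrt(n - 3), the rate is 1 - Φ(1.96 - m) + Φ(-1.96 - m). For 0.5/0.5 and n = 200: m = 0.0582 × 14.04 = 0.816, giving 0.126 + 0.003 = 0.129.

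| dA / dX (SD) | r | Rate by formula, n = 200 | Simulated, site ignored | Simulated, site removed |
|---|---|---|---|---|
| 0 / 0.5 | 0.000 | 5.0% | 4.8% | 5.0% |
| 0.3 / 0.3 | 0.022 | 6.1% | 6.1% | 5.0% |
| 0.5 / 0.5 | 0.058 | 12.9% | 12.4% | 4.9% |
| 0.8 / 0.5 | 0.089 | 24.0% | not run | not run |
| 0.8 / 0.8 | 0.136 | 48.7% | 49.5% | 4.7% |
| 1.0 / 1.0 | 0.198 | 80.4% | 81.7% | 4.7% |

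The simulations used 10,000 runs per row. If no patient in the two arms were lost (n = 290, two thirds of 435), the formula gives 6.6%, 16.7% and 64.3% for gaps of 0.3, 0.5 and 0.8 SD in both scores.

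**Step 3: masking.** Suppose the within-site correlation is -0.25 (higher expectancy, less dryness) and both gaps are 0.8 SD in the same direction. The correlation ignoring site is (-0.25 + 0.158) / 1.158 = -0.079, so |m| = 1.12 and power is about 20%. Within site, |m| = 0.2554 × sqrt(196) = 3.58 and power is about 95%.

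**Step 4: moderation.** Simulated rejection of arm x AES when expectancy moderates nothing, with n = 200 and AES differing by 0.8 SD between sites:

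| True-sham effect at the two sites (SD) | No site term | Site main effect only | Site and arm x site |
|---|---|---|---|
| 0.5 and 0 | 9-10% | 9-10% | about 5% |
| 0.8 and 0 | 16-17% | 17-18% | about 5% |

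A site main effect leaves the problem where it was. Only the arm x site term removes it.

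**The case against.** Several points on the other side are sound.

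- **The plan does not say that the sites are pooled.** That is inferred from its silence on site. It is the natural reading, since no by-site analysis is described, but the sponsor may have intended otherwise.
- **Aim 5 does not rest on the correlation alone.** The moderation half uses mixed models. If the general covariate list applies to them, they adjust for planned parotid dose and for ethnicity, a plausible proxy for site in a Houston-Shanghai trial. This stands as to main effects. C.6 a does not expressly carry the list over to the expectancy models, however, and a main effect does not supply the missing interaction (step 4). Nothing in the list reaches the plain correlation.
- **Every site gap is assumed.** Some features of the plan would narrow an AES gap: anyone who has ever used acupuncture is excluded (C.2), and the AES is described as validated in both languages (section B and C.5 d). Neither shows that mean scores are equal across sites, but neither allows a large gap to be presumed. The 49% and 81.7% figures need gaps of 0.8 to 1.0 SD in both scores, for which the documents offer no anchor.
- **The analysis is called exploratory** and belongs to the last of five secondary aims.

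A reader might infer that any site difference would produce a false expectancy effect. The arithmetic does not support that: both scores must differ, and at 0.3 SD in each the rate is about 6%, close to nominal.

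**Conclusion.** The point holds in a limited form. For the prediction half of aim 5, the single named method ignores a variable that separates the patients by country, language and disease. The resulting bias is negligible up to gaps of about 0.3 SD in both scores, material from about 0.5 SD (12-13% false positives), and large at 0.8 SD (49%). These figures assume 200 patients and no within-site association, and the gaps themselves are unknown. For moderation, the inflation is to about 9-10% if AES differs by 0.8 SD and the true-sham effect is 0.5 SD at one site and nil at the other; it also needs both differences to be present.

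It would go too far to conclude that aim 5 cannot be answered, or that a site artefact is to be expected. The documents contain no data showing that either score differs between the centres. Severity is low: an exploratory secondary analysis is affected, and the randomised primary comparison is not.

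**What to change.** In C.6 a of the Final Protocol:

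1. Replace the plain correlation with an association estimated within site: regress follow-up XQ on baseline AES with site, arm and baseline XQ in the model, and report the AES coefficient. Site is the term that removes the confounding; arm and baseline XQ mainly add precision. A correlation computed within each site and then combined would also deal with site, but it is not the same analysis, because it adjusts for neither arm nor baseline XQ.
2. In the moderation models, include site and arm x site beside arm x AES, at least as a sensitivity analysis, and state which covariates from the general list these models carry.

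Cost: a change of wording before analysis, with no new data, since site is known for every patient. In the moderation models, site and arm x site take two degrees of freedom with two arms. They take three if standard care is kept in, which is possible because C.5 d has all participants complete the baseline AES. Estimates will be slightly less precise.

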## 2. RESEARCH STRATEGY

### A. Significance

The proposed research is important for several reasons. The salivary glands are uniquely sensitive to damage from irradiation, and the development of radiation-induced xerostomia is clearly related to the exposure of salivary tissue. Mean parotid radiation doses >35Gy result in permanent xerostomia for most patients with no meaningful likelihood for recovery (1). Reduction in salivary flow begins during the first few days of treatment, with an 80% decrease noted at 6 weeks. In addition to a decrease in volume, other quantitative changes noted are a decrease in salivary pH, an increase in viscosity, and a reduction of salivary constituents (i.e., immunoglobulins, buffering capacity, small organic molecules) (2, 3).

Due to the high prevalence of smoking in China (4), head and neck cancer rates are high. In China, the incidence of nasopharyngeal cancer (NPC) is higher than in Western countries (5, 6). Available statistics indicate that the incidence of head and neck cancers in Shanghai is 14.1/100K and 6.5/100K for men and women, respectively (7). Among these, approximately 1000 are treated annually with radiation therapy at Fudan Cancer Hospital, and almost all patients receiving radiation to the head and neck area develop xerostomia. Furthermore, in the United States, nearly 40,000 patients are diagnosed annually with head and neck cancer, and approximately 80% will receive radiotherapy (8). In FY08, more than 1000 patients diagnosed with head and neck cancer were seen at M. D. Anderson and 466 underwent radiation treatment.

During the past decade, several new strategies to prevent radiation-induced xerostomia have been investigated including: 1) improved targeting of the radiation beam through intensity-modulated radiation therapy (IMRT); 2) development of radioprotective agents such as amifostine, and; 3) new surgical techniques that involve relocation of the submandibular gland to the submental space before radiation treatment. These approaches are limited by several factors, including technological constraints, primary site of disease, and proximity of the tumor and involved lymph nodes to the parotid glands. Treatment for xerostomia is, at best, palliative for symptom relief. Several approaches, including saliva substitutes, chewing gum, lozenges, pilocarpine, and amifostine, have been attempted with limited results and low acceptance due to unpleasant side effects (9-17). Also, pilocarpine is not commonly used in China, where there is currently no widely accepted treatment for radiation-induced xerostomia. Although IMRT has been shown to reduce the incidence of late grade 2 xerostomia (18, 19), all patients do not receive IMRT, and it is not commonly available in many areas of China. Also, IMRT only partly spares the parotid glands and minor salivary glands within the oral cavity; thus, the development of xerostomia remains high (20-24). In a pilot trial at M. D. Anderson investigating the use of acupuncture to treat radiation-induced xerostomia (25), most participants had received IMRT, yet these patients still benefited from the acupuncture treatment (see Preliminary Studies C.8).

Acupuncture therapy has been practiced in China and other regions for thousands of years. According to the World Health Organization, it is used in at least 78 countries worldwide (26). The therapeutic effects of acupuncture treatment range widely, and Eastern cultures commonly use it for a variety of conditions from alleviation of general fatigue to the treatment of specific diseases (27). According to traditional Chinese medicine (TCM), acupuncture points are specific sites along meridians that are related to internal organs. Modern anatomical and physiological studies have found that these acupoints are areas on the skin surface with lower electrical resistance and increased conductance compared to that of their

immediate environment (28). Some studies have shown that acupuncture points correspond to peripheral cranial and spinal nerve endings (29). To stimulate these points, the most common technique remains penetration of the skin by thin, solid, metallic needles, which are manipulated manually or by electrical stimulation.

From a TCM perspective, loss of body fluids is considered a Yin deficiency syndrome (30). Although Yin deficiencies may be related to various organ systems, xerostomia is primarily considered a deficiency of the Stomach and/or Kidney Yin. Individual patients may concomitantly exhibit signs and symptoms of Lung Yin, Heart Yin, and/or Qi-Blood deficiencies as well as any number of other underlying imbalances. Most xerostomia studies conducted to date that base acupuncture point selection on classical TCM theory have been designed to address Stomach and/or Kidney Yin deficiency and “clear heat.” Heat in TCM dries body fluids and can occur in both excess and deficiency states. In xerostomia patients, excess heat is caused from the radiation and deficiency heat is caused by the underlying Yin imbalance.

A number of positive clinical trials (25, 31-41) have been conducted examining the use of acupuncture to treat radiation-induced xerostomia (See Appendix C for a Table summarizing the findings). However, two systematic reviews (42, 43) indicated that most of these trials have been small and methodological rigor is often lacking, indicating the need for larger randomized trials.

Neuronal substrates involved in changes in saliva production after stimulation of acupuncture point LI-2 have been explored by Deng and colleagues (44) using functional magnetic resonance imaging. In this randomized, sham-controlled cross-over trial, 20 healthy volunteers received both true and sham acupuncture in random order. Unilateral manual acupuncture was associated with bilateral activation of areas of the brain where gustatory, olfactory, visual stimuli and signals from expectation/suggestion are integrated. Sham acupuncture did not produce this effect. Furthermore, true acupuncture caused significantly more saliva production in participants than sham acupuncture ( $p=0.02$ ), and there was a positive correlation ( $r=0.63$ ) between the amount of saliva produced and changes in the regions of interest volume. This brain imaging trial, along with the other small positive studies, suggests further research is needed in this area. Finally, there needs to be a better understanding of the putative biological mechanisms involved in the treatment of xerostomia using acupuncture.

This trial seeks to improve scientific knowledge regarding the benefits of acupuncture for xerostomia by conducting a multi-center, placebo-controlled, phase III clinical trial of acupuncture to prevent xerostomia. In addition to self-report measures of xerostomia and quality of life (QOL), we will quantify changes in saliva flow and examine potential mechanisms through quantitative assessment of changes in saliva following acupuncture treatment. Although other studies (2, 3) have evaluated salivary viscosity, pH, and buffering capacity related to xerostomia, changes in these measures in response to acupuncture have not been investigated. We will also expand data from previous acupuncture studies (38, 39) reporting changes in objective indices by measuring changes in calcitonin-gene-related peptide (CGRP) and vasoactive intestinal polypeptide (VIP).

